**Methods:**

For the primary objective of studying feasibility of the integrated mhGAP/IPT-G depression care in MCH service context for adolescent perinatal depression, we will recruit 90 pregnant adolescents to a three-arm pilot intervention (unmasked) trial study (IPT-G Full, IPT-G Mini, and wait-list control in the context of mhGAP care). Pregnant adolescents ages 13–18, in their 1st-2nd trimester with a depression score of 13 and above on EPDS would be recruited. Proctor’s implementation evaluation model will be used. Feasibility and acceptability of the intervention implementation and size of effects on mental health and family functioning will be estimated using mixed method data collection from caregivers of adolescents, adolescents, and health care providers. In the two sub-studies, stakeholders representing diverse perspectives will be recruited and focus group discussions data will be gathered. For aim 2, to build capacity for mhGAP-approach of adolescent depression care and research, the implementation-capacity training manual will be applied to train 20 providers, 12 IPT-G implementers/health workers and 16 Kenyan researchers. Acceptability and appropriateness of the training approach will be assessed. Additional feedback related to co-located service delivery model, task-shifting and task-sharing approach of IPT-G delivery will be gathered for further manual improvement.

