#### Intervention implementation

Participants will be randomly assigned to IPT-G Full, IPT-G Mini, and wait-list control using computer random generator by research staff (*n* = 15 for each arm, 45 per cohort).
The IPT-G Full and Mini groups will receive the assigned interventions (8 vs. 4 sessions) developed from Aims 1 and 2 (including a perinatal depression educational material/handout). To avoid contamination, intervention for the IPT-G Full and Mini versions will be carried out by 2 separate implementation teams (2–3 facilitators in each team) follow the assigned manual/protocol. Figure 2 provides intervention contents for the Mini version, in comparison to the recommended Full version.The Control will receive standard care (with referral) and perinatal depression educational materials for safety concerns. They will receive IPT-G Mini after the post implementation assessment is completed.

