#### Analysis plan for the feasibility outcomes

Data collected through 2 cohorts will be analyzed. Quantitative analysis will be focused on examining the following questions:
Examine acceptability, appropriateness, usefulness, engagement, and fidelity for both full and mini versions of integrated mhGAP/IPT-G intervention implementation using task-shifting/sharing approach in MCH contexts.Examine MCH service quality change patterns before and after implementation of the mhGAP/IPT-G model will improve.Examine whether pregnant adolescents in the IPT-G will have better outcomes relative to control, but high impacts/effect size for the IPT-G Full version.

The following stop-go criteria will be used to determine whether to proceed to the main trial: the recruitment proceeds well so that the first IPT-G cohort can proceed by the end of the first month of the specified recruitment period. The IPT therapists that is the trained CHVs and nurses demonstrate adequate levels of treatment fidelity to the WHO IPT-G checklist adherence available in the manual and 70% of participants attend at least 5 of the available sessions in the course of their treatment and 80% are successfully followed up at primary endpoint.

Quantitative analysis for *implementation outcomes* will be based on data collected throughout the implementation period, and analyzed separately for each time point as well as jointly to create overall summary scores. Analysis for the *MCH service outcomes* will be based on pre-post intervention data using *paired-t tests* and repeated measures. We will examine patterns separately and jointly for two MCH clinics. Analysis for *estimating size of impact* on mental health (depression) and family functioning will be based on multi-level modeling, adjusting for family/group nesting effects. Post-intervention effects/impacts will be estimated as a function of baseline levels of the corresponding outcome variables and intervention status. Effect size (regardless the statistical testing significant level) will be computed. *Quantitative data* for implementation outcomes, MCH service outcomes, and adolescent mental health effectiveness outcomes will be examined separately.

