## Discussion

Pregnant adolescents in SSA are burdened by significant unmet health needs including lack of access to mental health services. This study seeks to enrich WHO’s mental health depression intervention by carefully studying potential implementation challenges and identifying and integrating culturally and developmentally sensitive implementation strategies that fit primary care settings in Kenya. This study addresses intervention, service implementation, and public health research gaps for perinatal depression in adolescents in LMICs by utilizing mhGAP-IG, and WHO recommended IPT-G. Considering system, leadership, research strengthening needs (see the description of the Action Plan in Background section) and needs for cost-effective and culturally sensitive depression interventions for pregnant adolescent in Kenya, we will apply a multi-disciplinary/stakeholder partnership approach to adapt and test mhGAP-IG depression intervention guideline/tools and IPT-G to be implemented in MCH clinics. Three key implementation research questions will be studied: (i) how to improve fit of the mhGAP-depression intervention model (including IPT-G) for pregnant adolescents in Kenya, (ii) how to effectively integrate task-shifting/sharing and collaborative strategies with MCH clinical workflow to implement mhGAP depression intervention for pregnant adolescents in MCH settings, and (iii) whether the adapted mhGAP and IPT-G are feasible, appropriate, acceptable, and useful in addressing perinatal depression in adolescents. Considering the demand-resource challenge, this study will also explore related strategies, such as study feasibility of applying Long and Mini version of IPT-G (i.e., 8 vs. 4 sessions) and other potential cost-effective task shifting/sharing strategies (e.g., family/adolescent peer co-lead implementation approach). The IPT-G Full version includes 3 phases of intervention: defining “interpersonal inventory (through examining the interpersonal context of depression and exploring the links between the depression and their environment), making changes (through communication analysis, role play and effective strategies to improve social support and relationships), and identify successes and plan for independent application of IPT principles [41]. It has been found to be highly acceptable and efficacious to perinatal women in LMIC populations [42]. Considering the demand-resource gap, it is critical to consider offering IPT-G Mini version. The development of the shorter (Mini) version will be based on recent work [43, 44] that has developed a three-sessions version. We will adapt and study the fit of the Full and Mini version in MCH contexts (under sub-study 1). After sub-studies 1 and 2 there may be possibilities of reviewing and amending the study protocol to bolster the implementation model and research design for the pilot feasibility trial. In such a scenario, the PI after approvals from the mentors and technical advisory group would make amendments to the IRB.

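### The stop-go rule needs 70% of participants to attend at least 5 sessions, but the Mini arm has only 4, so the rule cannot be met as written

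*Protocol article*

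**What the plan says.** The section Analysis plan for the feasibility outcomes introduces the progression rule with "The following stop-go criteria will be used to determine whether to proceed to the main trial". Its parts are recruitment, therapist fidelity, attendance and follow-up. The attendance part is that "70% of participants attend at least 5 of the available sessions in the course of their treatment". It names no arm, defines no denominator and gives no separate count for the shorter version.

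The number of sessions is fixed elsewhere in the same article. Intervention implementation says: "The IPT-G Full and Mini groups will receive the assigned interventions (8 vs. 4 sessions". The Discussion repeats the same counts: "study feasibility of applying Long and Mini version of IPT-G (i.e., 8 vs. 4 sessions". Of the wait-list controls, Intervention implementation says: "They will receive IPT-G Mini after the post implementation assessment is completed".

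Allocation is equal ("15 for each arm, 45 per cohort"), over two cohorts. The abstract gives the total: "we will recruit 90 pregnant adolescents to a three-arm pilot intervention".

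**The concern.** A participant who is offered 4 sessions cannot attend 5. The attendance criterion is a single fixed count for all participants, yet only one of the three arms is offered that many sessions. The words about available sessions do not rescue it, because the count stays at 5 whatever number is available.

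In a pilot, the progression rule is the main decision the study produces. If this part cannot be satisfied, there are two outcomes, and both are bad. Either the rule is applied literally and returns stop regardless of the data, or someone redefines the denominator once attendance is known, which defeats the purpose of setting the rule in advance. The rule also provides no usable attendance test for the Mini version. Mini is the version put forward in the Background and Methodology as the answer to limited clinic resources, and its comparison with Full is what the pilot is meant to show can be done.

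**Working it through.** **Inputs**
- Sessions offered: Full 8, Mini 4 (Intervention implementation; repeated in the Discussion).
- Sessions offered to controls: 0 before the post-implementation assessment, then the Mini course of 4 (Intervention implementation).
- Allocation: 15 per arm in each of two cohorts (Intervention implementation; Study procedure).
- Criterion: at least 5 sessions, reached by 70% (Analysis plan for the feasibility outcomes).

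**Reproducing the plan's sample size.** 15 per arm × 2 cohorts = 30 per arm, and 30 × 3 arms = 90. This agrees with the stated total, so 30 per arm is the right basis for what follows.

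**Highest attainable share.** Assume perfect attendance: everyone attends every session offered. Then

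highest share = (participants in arms offering 5 or more sessions) / (participants in the denominator).

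Only Full offers 5 or more, so the numerator is 30 whenever Full is included. The number needed is 0.70 × denominator.

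| Denominator | n | Can reach 5 sessions | Highest share | Needed for 70% |
|---|---|---|---|---|
| Mini only | 30 | 0 | 0% | 21 |
| Full + Mini | 60 | 30 | 50% | 42 |
| All three arms | 90 | 30 | 33.3% | 63 |
| Full only | 30 | 30 | 100% | 21 |

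The all-arms row is the same whether controls are counted at 0 sessions or at the 4 they receive later, since both are below 5.

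**Could the split between arms rescue the pooled criterion?** With perfect attendance the pooled share is nFull/(nFull + nMini). For this to reach 0.70, nFull/nMini must be at least 0.70/0.30 = 2.33. The planned ratio is 30/30 = 1. Within one cohort the ceiling is the same: 15/30 = 50%.

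**What the count means as a proportion.** 5 of 8 is 62.5% of the Full course. The same proportion of 4 Mini sessions is 0.625 × 4 = 2.5, which rounds up to 3. A criterion set as a share of scheduled sessions is therefore attainable in both arms.

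**The case against.** The best defence is that the criterion was meant for the Full arm only. A count of 5 suits an 8-session course. The neighbouring fidelity criterion refers to the WHO IPT-G checklist, and the article elsewhere calls Full the WHO-recommended version. On that reading the rule is attainable, with 21 of 30 needed. But the restriction is not written, and the same section opens by proposing to examine engagement and fidelity for both versions. If the reading were adopted, progression would carry no attendance test for Mini.

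Second, counting controls is strained, since the criterion speaks of attendance during treatment and they receive no IPT-G in the trial period. That is fair. The 50% ceiling for the two active arms is the main figure and the 33% ceiling is secondary. Both fall short of 70%.

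Third, Mini's feasibility is measured elsewhere. Session participation is recorded in both active arms, and Table 1 has a 70% exposure criterion that is not tied to a session count. This stands as far as it goes: Mini attendance will be known. It does not repair the stop-go rule.

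Fourth, the Discussion allows for amending the protocol after the sub-studies, and the other stop-go criteria are loosely worded, so an automatic stop is the literal reading rather than a certain outcome. A possible amendment does not correct the present text, however, and this criterion carries a definite number.

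Finally, any replacement threshold is a choice. With a 60% rule, rounding asks for 62.5% of sessions in Full (5/8) but 75% in Mini (3/4). That is true, and it is why the threshold below is only an example.

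**Conclusion.** The concern holds. As worded, the attendance criterion conflicts with the session counts in the same article and cannot be met: at most 50% of the two active arms, or 33% of all randomised, can attend 5 sessions, against 70% required. The result rests on the stated 8 and 4 sessions, equal allocation with 30 per arm, and perfect attendance, which is the case most favourable to the plan. It depends on Mini participants being in the denominator, which is the plain meaning of the text. The only reading that avoids it, Full alone, is unstated and would leave Mini without an attendance test in the progression rule. Allocation, data collection and effect estimation are not affected. The damage is to the go/no-go decision, and the criterion must be corrected before it is used.

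**What to change.** Replace the single count with a criterion for each active arm, expressed as a share of the sessions scheduled in that arm, and state that wait-list participants are not in the denominator. For example: in each of the Full and Mini arms, at least 70% of those randomised (0.70 × 30 = 21) attend at least 60% of their scheduled sessions. That is 5 of 8 for Full (0.60 × 8 = 4.8, rounded up), which keeps the protocol's own count, and 3 of 4 for Mini (0.60 × 4 = 2.4, rounded up). The investigators may prefer another threshold. What matters is that the arm and denominator are named and the count is attainable in each. It would also help to say whether the arms are judged separately, so that one version could go forward without the other.

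The cost is one sentence in the stop-go criteria. Session attendance is already to be collected, so no new data are needed.

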**Fig. 1 Fig1:**
[figure not shown]
CONSORT for mhGAP/IPT-G Randomized Pilot Feasibility Study

**Table 1 Tab1:** Summary table the pilot feasibility trial

Objectives	Outcomes	Criterion for success	Method for analysis	Estimate of effect
Primary feasibility	Demonstrate that the method of RCT feasible in MCH clinical service context	70% of pregnant adolescent-caregiver-health care workers that are exposed to content of the intervention; 80% of data collection performed as planned;	Quantitative analysis for implementation outcomes will be based on data collected throughout the implementation period, and analyzed separately for each time point as well as jointly to create overall summary scores. Analysis for the MCH service outcomes will be based on pre-post intervention data using pair-t tests and repeated measures. Quantitative data for implementation outcomes, MCH service outcomes, and adolescent mental health effectiveness outcomes will be examined separately. Qualitative data will be transcribed and analyzed using similar techniques described in Aim 1. We will review all focus group discussion data and use grounded theory approach to search for emerging themes using open and axial coding.	Depression and family functioning will be based on multi-level modeling, adjusting for family/group nesting effects. Post-intervention effects estimated as a function of baseline levels of the corresponding outcome variables and intervention status.
Secondary outcomes	a) Identification of barriers and facilitators to mhGAP/IPT-G implementation in MCH context b) Capacity building of MCH personnel, researchers and select MOH and County health partners c) Adaptation of mhGAP/IPT-G	a. Identification of select mhGAP informed barriers to care and adaptation of mhGAP and IPT-G for this context b. Capacity building will significantly improve trainees’ (nurses and community health workers) knowledge and skills in implementation research and delivering of depression intervention. c. Adapted manual for IPT-G and algorithm for mhGAP-IG for depression for pregnant adolescents	Qualitative and ethnographic methods including mixed methods using D& I and attitudes to EBI and adolescent friendly health services Pre and post training interviews and acceptability and satisfaction the trainings Knowledge and fidelity trainings on mhGAP/IPT-G	N/A

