#### Feasibility evaluation measures and procedure

To evaluate feasibility of the mhGAP-IG/IPT-G implementation model in the MCHs, a mixed methods data collection approach will be applied and data will be collected from multiple sources (i.e., implementers, MCH leaders, adolescent mothers and their family members) to minimize data collection bias. As described above, the *Conceptual model of Implementation Outcomes* [56] is applied to guide the construct selection for the implementation feasibility and impact estimation. Feasibility of the mhGAP/IPT-G mental health service delivery model will be assessed using three indicators: fidelity (i.e., % of sessions is delivered with > 80% of contents), level of engagement (e.g., % reach targeted population, % participating in intervention sessions), quality of implementation (e.g., acceptability, appropriateness, usefulness, satisfaction of the mhGAP/IPT-G service model), and perceived mental health service (e.g., mental health service quality, MCH climate). Feasibility of applying a trial design for mhGAP/IPT-G impact evaluation in MCHs will be assessed using two indicators: % of adolescent-caregiver pairs that are exposed to intervention contents within the assigned condition; and % of data collection performed as planned. Impacts/effect size estimation for the IPT-G Full and Mini versions (the secondary outcomes) will be assessed for adolescents’ mental health and family functioning outcomes. Both quantitative data and qualitative data will be collected. Qualitative data will be collected through focus groups (2 groups for each intervention arm) at the end of implementation cycle. Tables 1 and 4 lists the feasibility outcomes measures and sources of data collection (under implementation feasibility, mental health service outcomes, and trial design feasibility and effect size estimation). Implementation feasibility outcome data, collected from the MCH staff/intervention implementers and adolescents who participated in the two intervention arms (IPT-G Full and Mini), will be gathered after each group session throughout the two implementation periods. For effect-size estimation, all study participants will complete a baseline (Time 1) interview (on mental health and family functioning outcomes) before randomization and intervention implementation, followed by a 1- or 2-month implementation period (2 months for the IPT-G Full and 1 month for the IPT-G Mini). Only when a participant is physically unwell, or has to terminate due to a pregnancy related emergency or any other severe mental health issue will their participant grouping be unblinded and an appropriate referral made. They will receive a post-intervention interview assessment at the end of implementation cycle (Time 2, about 3–4 months after the Time 1). To facilitate coordination of program implementation activities, participating MCH will be provided with two tablets and a small incentive which could offset implementation costs.

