#### Sample size

A randomly selected sample of 90 adolescent-parent dyads will be recruited. It has been suggested that a minimum of 30 participants per group/arm is sufficient for individual IPT and IPT-G pilot studies based on similar intervention studies in LMICs [17, 18, 23].

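### The 80% follow-up go criterion names no denominator and sets no minimum per arm, so it does not guard against retention that differs between arms

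*Protocol article*

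**What the plan says.** The rule is in the protocol article under *Analysis plan for the feasibility outcomes*. It opens with "The following stop-go criteria will be used to determine whether to proceed to the main trial" and then lists recruitment pace, therapist fidelity, session attendance and follow-up. The follow-up part reads "80% are successfully followed up at primary endpoint". No arm, cohort or denominator is named.

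Table 1 has a related success criterion, "80% of data collection performed as planned", which is not split by arm either. Under *Feasibility evaluation measures and procedure*, "Feasibility of applying a trial design for mhGAP/IPT-G impact evaluation in MCHs will be assessed using two indicators": the share of adolescent-caregiver pairs exposed to content within their assigned condition, and the share of data collection done as planned. Neither is a retention threshold by arm.

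On the design, the abstract says "we will recruit 90 pregnant adolescents to a three-arm pilot intervention (unmasked) trial study", and *Intervention implementation* gives "15 for each arm, 45 per cohort". The two cohorts are the two clinics. Of the controls, that section says "They will receive IPT-G Mini after the post implementation assessment is completed". *Methodology for primary pilot trial* makes the feasibility of an RCT design for comparing the impacts of Full and Mini part of the primary goal. Effect-size estimation is the secondary goal there, although a note to Table 2 calls the effectiveness outcomes primary.

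**The concern.** The three arms have different reasons to return for Time 2, about 3–4 months after baseline. Controls have had no sessions but are offered Mini once they have been assessed. Full participants have finished about two months of treatment, and Mini participants about one month. Everyone knows their allocation. The article gives no basis for predicting which arm would be retained worst, and that uncertainty is itself a reason for the pilot to look.

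A feasibility pilot for a three-arm comparison should be able to find that one arm does not come back. An overall percentage can be met while one arm falls well short, because good retention in the other two makes up for it. The rule would then report success on follow-up for a design whose between-arm comparisons are exposed to selective loss, and the main trial would inherit the problem.

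**Working it through.** **Inputs from the article.** 15 per arm, 3 arms, 2 cohorts; threshold 80%; Full has 8 sessions and Mini has 4. The article states no expected retention, so every retention rate below is an assumption.

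**Sample size.** 15 × 3 × 2 = 90, or 30 per arm. This reproduces the article's total. The size rests on precedent ("a minimum of 30 participants per group/arm is sufficient for individual IPT and IPT-G pilot studies"), so there is no power calculation or dropout allowance to check.

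**What the threshold allows if the denominator is all 90.** 0.80 × 90 = 72 followed up, so 18 may be lost.
- 27 + 27 + 18 = 72 passes, with arms at 90%, 90% and 60%.
- 30 + 30 + 12 = 72 passes, with one arm at 12/30 = 40%. This is the extreme.
- For an arm to keep 14 or fewer (more than half lost), the other two must keep at least 72 − 14 = 58 of 60 (96.7%).
- If exactly 18 losses fell at random across arms, the hypergeometric probability that some arm loses 16 or more is about 2 in 10 million. The extreme therefore needs strong arm-specific dropout.

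**If the denominator is the 60 treated participants.** 0.80 × 60 = 48, so 12 may be lost, up to 12/30 = 40% of one arm. Control retention is then not assessed at all.

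**Chance of meeting the follow-up rule.** The number followed in each arm is Binomial(30, p), independent across arms, and the distribution of the total is found by exact convolution. The second column requires a total of at least 72. The third also requires at least 21/30 (70%) in every arm.

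| Assumed true retention by arm | 80% overall | 80% overall and 21/30 in each arm |
|---|---|---|
| 92 / 92 / 60% | 0.697 | 0.174 |
| 95 / 95 / 60% | 0.865 | 0.176 |
| 92 / 92 / 40% | 0.10 | below 0.001 |
| 85% in all arms | 0.926 | 0.914 |
| 90% in all arms | 0.999 | 0.998 |

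A floor of 80% (24/30) in every arm would be too strict at this size: with true retention of 85% everywhere, it passes with probability only 0.61.

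**Precision of a between-arm effect size.** The approximate 95% half-width in SD units is 1.96 × √(1/n₁ + 1/n₂), ignoring group clustering:
- 30 vs 30: 1.96 × √(2/30) = 0.51
- 24 vs 24: 1.96 × √(2/24) = 0.57
- 12 vs 30: 1.96 × √(1/12 + 1/30) = 0.67

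Even the extreme split costs only moderate precision. What remains is bias, and the article gives nothing from which to calculate it.

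**The attendance clause in the same sentence.** It asks for 70% of participants to attend at least 5 sessions. Mini has 4 sessions, and controls have none before Time 2. Only the 30 Full participants can qualify: at most 30/60 = 50% of those treated, or 30/90 = 33% of all. On either of those readings, no overall go is possible.

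**The case against.** The strongest objection is that a single retention threshold in a 90-person pilot is an ordinary choice, and that the article does not call it pooled. Arm-level information is also not hidden. Exposure is assessed within the assigned condition, engagement is examined for both Full and Mini, a monitoring board sees interim comparisons of the arms, and there is a CONSORT figure. All arms attend regular clinic visits, and the offer of Mini after Time 2 gives controls a reason to return. Follow-up alone does not produce a go either, because the criteria are joined.

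Much of this stands. The denominator is open, so reading the rule as 80% of all 90 is an interpretation, though the natural one. The direction of any imbalance is unknown. The follow-up clause also cannot be judged entirely apart from the attendance clause. But none of the items listed is a retention threshold by arm, and on either denominator one arm can fall far below the others while the follow-up criterion is met. Nor is this detail left to an analysis plan, since the article itself states the rule and its figure.

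A reader might go further and infer that a go could readily be declared with one arm having lost most of its participants and the effect sizes worthless. The documents do not support that. Losing more than half of an arm needs near-complete retention in the other two, and at 92/92/40% the rule passes only about one time in ten. The half-width grows from 0.51 SD at full retention to 0.67 SD at worst. Bias is possible but not shown.

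**Conclusion.** The point holds as a gap in a stated decision rule. The follow-up criterion lacks a denominator and a minimum per arm, and so does not protect the comparison whose feasibility the pilot is meant to test. The realistic size of the problem is an arm at about 60% retention: with the other two at 92%, the criterion is met with probability about 0.70, against 0.17 once a 21/30 floor is added. These figures assume all 90 as the denominator, 30 per arm, independent dropout and the retention rates shown, none of which the article supplies. They describe the follow-up criterion only and not an overall go, which also depends on an attendance clause that the Mini arm cannot meet as written. The change is worth making before the pilot data are seen.

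**What to change.** Reword the follow-up criterion along these lines: at least 80% of all randomised participants complete Time 2, and at least 70% (21 of 30) do so in each arm. Alternatively, keep 80% overall as the bar and treat any arm below 70% as an amber result that requires a revised retention plan before the main trial. Report Time 2 counts by arm and by clinic in either case. The 70% figure is a suggestion and has no source in the article; the sponsor may choose another floor and should give its reason.

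The cost is one sentence and no new data. The rule becomes slightly stricter: the chance of passing falls from 0.926 to 0.914 if true retention is 85% in every arm, and from 0.999 to 0.998 if it is 90%.

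Separately, the attendance clause under *Analysis plan for the feasibility outcomes* (at least 5 sessions) and the 4-session Mini arm under *Intervention implementation* must be reconciled, and the participants to whom the clause applies must be stated. Until then, a better follow-up criterion does not by itself make the go decision workable.
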